**E. HIV-positive population**

It is estimated that 4% of the annual birth cohort (approximately 900 children) in Soweto will be HIV-seropositive. The effect of the vaccine on the following outcome variables in children enrolled in the study who are confirmed to be HIV-infected will be evaluated.

1. Vaccine-serotype invasive disease. The analysis will include the comparison of disease rates and time to first episode of disease (from 14 days after the third dose of vaccine) between the vaccinated and control children. A sensitivity analysis will be performed to examine the robustness of the vaccine efficacy estimate with respect to the assumption of equal follow-up time in the two groups.

2. Radiologically-confirmed hospitalized pneumonia. The analysis will include the comparison of event rate and time to first event between the two groups. An analysis to compare the number of children with at least one event will also be performed.

3. All invasive pneumococcal disease, including nonvaccine serotypes. The analysis will be done as described in Section IX.C.1 above.

4. Pneumonia-related mortality. Mortality resulting from pneumonia will be analyzed using the life table method and the survival curves of the vaccinated and the control group will be compared using the log rank test.

5. All cause mortality. The all-cause mortality will be analyzed using the life table method and the survival curves of the vaccinated and the control group will be compared using the log rank test.

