The current estimate of the incidence of invasive pneumococcal disease in children under the age of 2 years in Soweto is 160/100,000 child years [12]. Assuming that 70% of the disease cases are due to the vaccine serotypes, the vaccine-serotype disease rate is 112 cases per 100,000 child years. Based on this estimate of disease rate and the assumption that the true vaccine efficacy is 70%, approximately 19,231 child years follow-up per treatment group will be needed to accrue 28 cases of vaccine-serotype disease in HIV-uninfected children. The annual birth cohort in Soweto is approximately 24,000 infants, 4% (960) of whom would be expected to be HIV-infected. Allowing for loss to follow-up, the entire birth cohort over a two year period will be recruited to reach the targeted enrolment goal. The study is expected to accrue 28 cases of vaccine-serotype disease in HIV-uninfected children in approximately 32 months. Approximately 29,533 child years of follow-up per treatment group, expected in approximately 39 months, will be needed to accrue 43 cases. A more accurate estimate of the disease rate is expected to be obtained prior to the start of the study from the prospective cohort study currently underway in Soweto.

The rate of hospitalized pneumonia (Primary Outcome ‘2') will be compared between the treated and the control group using a Poisson regression, with age category and calendar month of the third dose (season category) as possible stratification variables. An estimate of the rate reduction and its confidence interval will be obtained from the Poisson regression. Multiple events of an individual will be included in the rate estimates. The null hypothesis is that there is no rate reduction and will be tested based on the Poisson regression with a two-tailed  = 0.05. An analysis to compare the number of children with at least one event between the two groups will also be performed.

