**F. Estimated study mortality**

Using statistics from Chris Hani Baragwanath Hospital, 50% (450) of the HIV-infected children enrolled in the study will die within the first year of life. The infant mortality rate for children between 6 weeks and 2 years of age in Soweto is approximately 10/1000, suggesting that an additional 220 children will also die during one year of follow-up. In total, an estimated 670 children in the study cohort will die per annum.

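### Single-cause life-table curves for pneumonia death in HIV-infected children overstate pneumonia mortality in each arm when about half the children are expected to die of any cause; cumulative incidence would correct this

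*Protocol*

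**What the plan says.** Protocol section IX.E (HIV-positive population) lists two mortality outcomes.

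- **Item 4** concerns death from pneumonia: "Mortality resulting from pneumonia will be analyzed using the life table method". A log-rank test then compares the curves of the two arms.
- **Item 5** treats all-cause death as a separate outcome, with the same life table and log-rank test.

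Section IX.F gives the expected mortality: "50% (450) of the HIV-infected children enrolled in the study will die within the first year of life". That figure covers every cause of death.

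Section V.G ends a child's follow-up at death, whatever the cause. The protocol does not mention competing causes of death, cumulative incidence or a multiple-decrement table, and does not say how a death from another cause enters the item 4 analysis. The analysis serves the fifth secondary objective for HIV-infected children in section II.B, the effect of vaccination on pneumonia-related and all-cause mortality.

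**The concern.** Take a survival curve for one cause of death, with follow-up ending at any death. The usual construction counts a child who dies of septicaemia, gastro-enteritis or other HIV disease as withdrawn at that moment. The life table then behaves as if that child could still die of pneumonia later. The child cannot, so other-cause death is a competing event and not ordinary censoring. One minus the curve estimates a pneumonia risk in a setting where nobody dies of anything else, which is higher than the risk these children face.

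With rare deaths the difference would be negligible. Here the protocol expects very high mortality, and Appendix 1 shows many hospital deaths under diagnoses other than pneumonia. At stake are the arm-level pneumonia mortality in the highest-mortality group and any absolute benefit read off the two curves. The curves would also be hard to set beside the all-cause result of item 5, because risks estimated by censoring each cause in turn add up to more than the all-cause risk.

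**Working it through.** **The plan's own figures.** Section IX.E: "It is estimated that 4% of the annual birth cohort (approximately 900 children" are HIV-positive. Section IX.F: 0.50 × 900 = 450 deaths among them, plus 220 others, gives 670: "In total, an estimated 670 children in the study cohort will die per annum". Both figures reproduce. Section IX.B gives a slightly different base, "4% (960) of whom would be expected to be HIV-infected", which would make it 0.50 × 960 = 480. This does not affect the argument, which uses only the 50%.

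**Inputs for the check**

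- All-cause one-year mortality M = 0.50 (section IX.F), with 0.30 as a lower alternative. The 0.30 is an assumption: children enrol at 5 to 12 weeks of age, item 4 states no time zero, and some of the first-year deaths may fall before it.
- Share s of deaths due to pneumonia. The protocol gives none for HIV-infected children, so s is assumed over 0.2 to 0.7. The deaths listed in Appendix 1 give one reference value: 93 + 0 + 1 + 3 + 15 + 53 + 0 + 86 + 48 = 299, of which 93 are bronchopneumonia, so 93/299 = 0.31. These are hospital deaths in all children, not only the HIV-infected.
- Constant cause-specific hazards over the year (assumption).

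**Formulas.** Total cumulative hazard H = −ln(1 − M).

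- Life table with other-cause deaths censored: 1 − exp(−sH) = 1 − (1 − M)^s.
- Cumulative incidence of pneumonia death: s × M.

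**One-year pneumonia mortality in one arm**

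| M | s | 1 − life table | Cumulative incidence | Excess (points) |
|---|---|---|---|---|
| 0.50 | 0.20 | 12.9% | 10.0% | 2.9 |
| 0.50 | 0.31 | 19.3% | 15.5% | 3.8 |
| 0.50 | 0.50 | 29.3% | 25.0% | 4.3 |
| 0.50 | 0.70 | 38.4% | 35.0% | 3.4 |
| 0.30 | 0.20 | 6.9% | 6.0% | 0.9 |
| 0.30 | 0.31 | 10.5% | 9.3% | 1.2 |
| 0.30 | 0.50 | 16.3% | 15.0% | 1.3 |
| 0.30 | 0.70 | 22.1% | 21.0% | 1.1 |

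**Additivity at M = 0.50, s = 0.31.** Censoring each cause in turn gives 19.3% for pneumonia and 1 − 0.5^0.69 = 38.0% for the rest. The sum is 57.3%, although 50% die.

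**Contrast between arms.** Assume a vaccine hazard ratio of 0.8 for pneumonia death, no effect on other deaths, M = 0.50 in controls and s = 0.31. H = 0.693.

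- Vaccine-arm pneumonia hazard: 0.8 × 0.31 × 0.693 = 0.172. Other-cause hazard: 0.69 × 0.693 = 0.478.
- Life table: 1 − exp(−0.172) = 15.8%. Difference: 19.3 − 15.8 = 3.5 points. Ratio: 0.817.
- Cumulative incidence: (0.172/0.650) × (1 − exp(−0.650)) = 12.6%. Difference: 15.5 − 12.6 = 2.9 points. Ratio: 0.815.
- Unrounded, the differences are 3.54 and 2.86 points, a distortion of about 0.7 points.
- Standard error of the difference in cumulative incidence, √[(0.155 × 0.845 + 0.126 × 0.874)/n]: 4.0 points at n = 150 per arm, 2.8 at 300 and 1.6 at 900. The distortion is therefore about 0.2, 0.2 and 0.4 standard errors.

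**The test.** In a simulation of 900 children (4,000 runs, s = 0.5, no true difference in the pneumonia hazard), the two-sided 5% log-rank test rejected in 4.7% of runs with equal other-cause hazards and in 5.0% with an other-cause hazard ratio of 0.7 between arms. Its size is correct.

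**The case against.** The strongest reply has four parts.

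1. **Censoring is inferred.** Item 4 names a life table and does not say what happens to other-cause deaths. A multiple-decrement table is also a life table, and such detail could sit in an analysis plan that is not shown. This stands as a limit on certainty. Survival curves and a log-rank test for one cause, with follow-up ending at any death, nevertheless point to censoring as the ordinary reading.
2. **The planned comparison is sound.** The only inferential step in item 4 is the log-rank test, and for the primary outcome the protocol expresses efficacy as a ratio. This stands in full. A reader might infer that the test, or the conclusion about relative effect, is biased. The calculations do not support that: the test keeps its size, and the risk ratio moves only from 0.815 to 0.817.
3. **The absolute difference is not a planned quantity, and its distortion is small against its uncertainty.** This also stands. Setting the arm-level excess against an arm-level standard error would make the problem look larger than it is for the treatment contrast.
4. **The inputs are at the upper end.** The 50% runs over the first year of life, not from an analysis origin. The protocol describes HIV testing for children with outcomes, in hospital or in the immunogenicity subset, so 900 per arm, the whole two-year HIV-infected cohort, is unlikely to be the analysis size. The objective refers to hospitalised children. The 31% share is borrowed from all children, and 86 of the 299 deaths are coded only as HIV infection. These points affect the size of the excess, not its direction.

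A reader might also extend the point to items 1 and 2, which compare "time to first episode of disease (from 14 days after the third dose of vaccine" and time to first pneumonia event. Those items name no estimator for a curve, so nothing is stated wrongly there.

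**Conclusion.** The point holds for the arm-level curves of item 4. If other-cause deaths are censored, one minus the life table overstates the probability of pneumonia death in both arms. The excess is about 3 to 4 points at 50% one-year mortality for pneumonia shares of 20 to 70%, and about 1 point at 30% mortality. An absolute difference taken from the curves is overstated too, by about 0.7 points in the worked example.

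This rests on the censoring reading, an assumed pneumonia share, constant hazards and an unstated time zero. Only the size depends on the last three. The primary outcomes and all-cause mortality (item 5) are untouched. Because the outcome is secondary and confined to a subgroup, the priority is low.

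**What to change.** Change section IX.E item 4 only.

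- Replace the life-table curves with the cumulative incidence of pneumonia death in each arm (Aalen-Johansen estimator), with death from any other cause as a competing event.
- Report the between-arm difference in cumulative incidence with its 95% confidence interval.
- Keep the log-rank test and label it a comparison of cause-specific hazards of pneumonia death.

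Item 5 stays as written. The cost is the wording of one item; the date and cause of death are already needed for items 4 and 5. The only downside is that the stated pneumonia mortality and absolute benefit come out slightly lower.

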**HIV-infected children (HIV ELISA positive and confirmed positive by PCR)**

1. To evaluate the efficacy of pneumococcal conjugate vaccine on the first episode of invasive pneumococcal disease, as previously defined, caused by vaccine serotypes in HIV-infected children receiving three doses of study vaccine per protocol.

2. To evaluate the efficacy of pneumococcal conjugate vaccine on the incidence of invasive pneumococcal disease caused by all serotypes in HIV-infected children who have received three doses of study vaccine per protocol.

3. To evaluate the efficacy of pneumococcal conjugate vaccine on the incidence of pneumonia in hospitalized HIV-infected children who have received three doses of study vaccine per protocol.

4. To evaluate the efficacy of two or more doses of the pneumococcal conjugate vaccine on the incidence of vaccine serotype-specific invasive disease and pneumonia in HIV-infected children.

5. To assess the impact of pneumococcal vaccination on pneumonia-related and all cause mortality and time to death of hospitalized HIV-infected children.

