**3. Vaccine Efficacy**

The statistical methods for calculating the efficacy of the nonavalent pneumococcal conjugate vaccine are described in Section XII. Vaccine efficacy will bedefined as the number of cases of culture-confirmed invasive pneumococcal disease or pneumonia in the HIV-negative group receiving the pneumococcal conjugate vaccine compared to the number of cases occurring in the placebo group. The study pediatricians will conduct daily surveillance for cases of severe pneumonia, as defined in Section VIII, at Chris Hani Baragwanath Hospital. In addition, a list of all cases of culture-confirmed pneumococcal disease will be obtained daily from the hospital microbiology laboratories. HIV testing will be performed in an anonymous manner for all children with study outcomes who are not tested for HIV during hospitalization. Those outcome cases with no HIV test results will be excluded from the efficacy analyses.

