**IX. Sample size and plan for analyses**

The study is designed primarily to evaluate the impact of the nonavalent pneumococcal conjugate vaccine in HIV-uninfected children. The cases in HIV-infected children will not be included in any primary analyses of vaccine efficacy as their outcome variables, disease incidence rates, expected vaccine efficacy, and expected follow-up time may all be different from that in the general population. The impact of the vaccine in this special population will be evaluated separately as a secondary objective. All case ascertainment will include HIV testing, in an anonymous and confidential manner. The HIV status will only be linked to clinical outcomes at the time of analysis. It will not be linked to any other health record of the child. Outcome cases for which HIV results are not available will be excluded from analyses.

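### Section IX.E plans mortality log-rank tests and time-to-first-event comparisons in HIV-infected children, but the protocol never identifies the randomised HIV-infected children at risk

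*Protocol*

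**What the plan says.** Protocol section IX.E sets its population as "children enrolled in the study who are confirmed to be HIV-infected will be evaluated". Items 4 and 5 plan life tables and log-rank tests for pneumonia-related and all-cause mortality; item 5 reads "The all-cause mortality will be analyzed using the life table method", with the two arms compared by that test. Item 1 includes a "comparison of disease rates and time to first episode of disease (from 14 days after the third dose of vaccine"), and item 2 a time to first pneumonia event.

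The matching objective (II.B, HIV-infected children, item 5; also in the Protocol Summary) names a different group: "pneumonia-related and all cause mortality and time to death of hospitalized HIV-infected children".

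On how HIV status is obtained, V.F.3 says "HIV testing will be performed in an anonymous manner for all children with study outcomes who are not tested for HIV during hospitalization", and the opening of section IX says "All case ascertainment will include HIV testing, in an anonymous and confidential manner". Section VI.E.2.b describes an HIV specimen for hospitalised study patients. Section V.F.2 adds anonymous testing of the immunogenicity subset to estimate seroprevalence. No HIV test at enrolment is described (sections IV, V.A, VI.A). Sections V.F.1 and VI.D seek deaths outside hospital through notifications and cemetery records, without describing an HIV test for them.

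**The concern.** A life table or log-rank test by arm keeps the protection of randomisation only if everyone in the target group is followed from a common origin, usually first dose or a fixed point after dose three. Here a child is known to be HIV-infected, in practice, only after being hospitalised or becoming an outcome case. HIV-infected children who stay well, or who die without ever being admitted, do not enter the curves.

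The vaccine is meant to reduce entry into the identified set, so the vaccinated and placebo children in it need not be alike. A real mortality benefit could disappear, or an apparent excess could arise from selection alone. That matters because section XIII.B asks the Safety Monitoring Committee to assess vaccine risk in HIV-infected children.

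**Working it through.** **1. The plan's own figure.** Section IX.F: 0.50 × 900 = 450 deaths a year in HIV-infected children, plus 220 others, gives 670. This reproduces. HIV-infected children account for 450/670 = 67% of expected deaths and the others for 220/670 = 33%.

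**2. Whose HIV status is known.**

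| Source | Who is tested | Randomised risk set? |
|---|---|---|
| V.F.3; opening of IX | Outcome cases | No: selected by the outcome |
| VI.E.2.b | Hospitalised study patients | No: selected by admission |
| V.F.2, IX.C item 4 | 200 children per lot, about 400 in all | No: anonymous, three doses at one clinic, bled at 18 weeks |
| V.F.1, VI.D | Deaths outside hospital | No HIV test described |

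At 4% prevalence the subset holds 200 × 0.04 = 8 HIV-infected children, or 400 × 0.04 = 16. Against about 2 × 900 = 1,800 in two annual cohorts, that is 16/1,800 = 0.9%.

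**3. Effect on the mortality ratio.** Let A be identified HIV-infected admissions in the placebo arm, k their case fatality, f the fraction of admissions averted by vaccine, and c the fatality the averted admissions would have had. Count deaths among admitted children, with equal arms.

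- Placebo deaths: kA. Vaccine deaths: kA − cfA.
- True ratio by randomised arm: T = 1 − fc/k.
- Ratio among admitted children: T/(1 − f).

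The proportion admitted cancels. Take k = 18% (pneumonia case fatality in HIV-infected children, section I.H). The protocol gives neither f nor c. I assume f = 20%, and use c = 0 together with 9% and 28% (the two Zimbabwean figures in section I.D) as low and high values.

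| c | T | Among admitted |
|---|---|---|
| 0% | 1.00 | 1.00/0.8 = 1.25 |
| 9% | 1 − 0.2 × 9/18 = 0.90 | 0.90/0.8 = 1.13 |
| 18% | 1 − 0.2 × 18/18 = 0.80 | 0.80/0.8 = 1.00 |
| 28% | 1 − 0.2 × 28/18 = 0.69 | 0.69/0.8 = 0.86 |

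With c = 0, f = 10% gives 1/0.9 = 1.11 and f = 30% gives 1/0.7 = 1.43. Over f = 10–30% and c = 9–28%, T runs from 0.53 to 0.95 and the ratio among admitted children from 0.76 to 1.21. The latter exceeds 1 only if averted admissions are milder than average (c < k).

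**4. Deaths that are never identified.** A log-rank simulation, with all rates assumed, took 900 HIV-infected children per arm, two years, 0.5 admissions per child-year, an admission rate ratio of 0.8 and a death hazard without admission of 0.1–0.6 per year.

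- Between 44% and 69% of deaths fell in children never identified as HIV-infected.
- When averted admissions carried no fatality, the hazard ratio was 1.01–1.03 in the full set and 1.08–1.19 from admission among identified children. Significant harm appeared in 15–30% of runs.
- When they carried 28% fatality and the hazard was 0.3, the ratios were 0.95 and 0.93. The distortion can thus go either way.

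**5. Time to first event.** If the set for item 2 consists of children with a pneumonia outcome, the curves compare when the event happened and not whether it did. For item 1 the set would also contain pneumonia admissions without vaccine-serotype invasive disease, so censoring remains, but entry still depends on admission.

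**6. Rate ratios.** Section IX.B takes the rate ratio as vaccine cases over placebo cases under 1:1 allocation. HIV status is then needed only for the cases. What remains is the equal follow-up assumption: item 1 has a sensitivity analysis for it, item 2 has none.

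**The case against.** Several points on the other side stand.

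- A reader might infer that all of IX.E fails, rates included. The documents do not support that. The case-count ratio does not condition on a post-randomisation event, item 2 already compares numbers of children with at least one event, and item 3 refers back to the IX.C.1 method.
- A reader might infer that HIV status is known only for hospitalised outcome cases. Section VI.E.2.b is wider, covering hospitalised study patients, and there is the immunogenicity subset. A child who dies at home may also have been tested at an earlier admission. The scope is unclear, but no reading of it gives the whole randomised set.
- A reader might infer that the curves contain almost no censored children. For item 1 that is wrong: section I.H reports bacteria in 28% of HIV-infected pneumonia and pneumococci as 50% of bacterial isolates, roughly 0.28 × 0.50 = 14%, so most would be censored for invasive disease.
- The bias may be small. If every admission is tested and the vaccine averts 20% of pneumonia admissions only, Appendix 1's 30.5% share for bronchopneumonia (all children, 1995) gives f = 0.20 × 0.305 = 0.061 and, with no deaths averted, a ratio of about 1.06.
- Objective 5 openly says hospitalised children, and it is secondary. That discloses the restriction but does not restore comparability, and IX.E does not repeat it.

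Nor can this be left to an analysis plan: no analysis wording recovers HIV status that the testing scheme does not collect.

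**Conclusion.** The point holds for IX.E items 4 and 5 and for the time-to-first-event parts of items 1 and 2. The group in objective 5 is selected after randomisation; the group in IX.E cannot be identified from the testing described. The mortality comparison is not protected by randomisation and could mask a benefit or suggest harm.

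The structural defect follows from the text. The sizes do not: they rest on assumed admission reductions and on the fatality of averted admissions, neither of which the protocol gives. A reader might infer that the plan will show false harm. That requires averted admissions to be milder than average, which no section states. The primary analyses and the vaccine/placebo rate ratios for disease in HIV-infected children are untouched.

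**What to change.** In IX.E:

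- Keep the count-based comparisons of HIV-infected cases by randomised arm. Keep item 1's sensitivity analysis for unequal follow-up and extend it to item 2, since IX.F expects 50% first-year mortality in this group.
- Drop the time-to-first-event comparisons in items 1 and 2, or label them descriptive.
- For all-cause mortality, make the by-arm log-rank comparison in all randomised children from the first dose, whatever their HIV status, using the in-hospital and out-of-hospital deaths already sought.
- Label mortality and survival analyses within hospitalised HIV-infected children descriptive.
- Reconcile objective 5 (Protocol Summary and II.B) with the population named in IX.E.

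Cost: wording changes to the objectives as well as the analysis section, with no new data collection. The all-children comparison answers a broader question than objective 5 and is diluted by HIV-uninfected children, about 220 of the 670 expected annual deaths. It does not give a mortality effect specific to HIV-infected children; that would need HIV status for every randomised child.
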